#### Component B: app design (sequential/non-sequential)

In-person parenting programmes, including PLH for Teens, typically deliver sessions in a sequential, weekly basis. ParentApp was originally designed to mirror this structure, i.e., content is delivered in a sequential order, whereby a new workshop is made available once every programme week. However, qualitative findings from the pilot study in South Africa indicated that some participants wanted to access content more flexibly and at their own pace. In addition, findings from this pilot suggested that participants typically used the app in multiple, short sessions. This suggests that a short, task-based approach may be an acceptable mode of delivery. Previous studies of digital parenting programmes have used both sequential access (e.g., [58, 59]) and open access methods (e.g., [60]). However, none have investigated which approach is more effective at engaging and retaining participants.

To better understand the impact that sequential versus non-sequential access to content has on engagement, we will test two versions of the app: 1) a workshop-based design where participants access content in a sequential and timed-bound manner, and 2) a module-based design where content is broken down into smaller tasks and participants can access content in a non-sequential manner. Thus, participants will be randomised across two component levels: 1) sequential workshop-based design and 2) non-sequential modular design. Based on participant feedback in the Preparation Phase, these two designs also differ visually: the sequential design will retain the amorphous cartoon figures and the non-sequential design will incorporate human-like illustrations.

#### Component C: digital literacy training (on/off)

A wide range of implementation and service-level strategies are routinely used to support engagement in parenting programmes. These include the provision of childcare, transport or financial aid, meals, and, seldomly, rewarding families with small gifts for attendance [61]. However, for digital parenting programmes, particularly in low-income settings where access to technology is not as widespread, digital literacy may be a key barrier to engaging with the intervention. This was highlighted in the Preparation Phase of this study, where technical challenges related to digital literacy, phone compatibility, network connectivity, and data access were frequent, particularly in the initial set-up phase. A recent systematic review investigating barriers and facilitators to engagement in 208 digital mental health interventions found that participants’ experience of technical challenges was a primary barrier to engagement, whereas digital literacy and previous positive experiences with the technology influenced the extent to which users engaged with the intervention; with higher digital literacy being associated with greater engagement [39]. The review also found that interventions that provided training on how to use the technology or the intervention achieved higher engagement. Digital literacy training may therefore be a critical implementation strategy to support engagement with digital interventions. This study will test the effectiveness of a digital literacy training as a strategy to maximise engagement with the app by randomising participants across two component levels: 1) receiving a brief, semi-structured digital literacy training at the group onboarding session, i.e., where participants are screened for eligibility, provide informed consent, and install the app on their phones, and 2) receiving no digital literacy training at the group on boarding session.

### Hypotheses

For the support component, we hypothesise that participants who receive WhatsApp groups will show higher levels of engagement compared to participants not receiving facilitated support.For the app design component, we hypothesise that participants who receive non-sequential module design will show higher levels of engagement compared to participants who receive sequential workshops.For the digital literacy component, we hypothesise that participants who receive the digital literacy training will show higher levels of engagement compared to participants receiving no digital literacy training.

### Study setting

The study will be conducted in low-income areas of Mwanza City, a port city next to Lake Victoria in Northern Tanzania. The study site was selected in consultation with research and implementation partners in Tanzania, the Tanzanian National Institute for Medical Research (NIMR) and local NGO Investing in Children and Strengthening their Societies (ICS).

### Participants and eligibility criteria

Recruitment will target socioeconomically vulnerable families from low-income communities, situated in peri-urban and urban regions of Mwanza City. Eligible clusters will be low-income neighbourhoods with appropriate sites for conducting onboarding sessions with approximately 40 participants. Examples of potential sites are community halls, schools, and community leaders’ offices. Eligible caregivers are: 1) age 18 or older, 2) the main caregiver of a teenager aged 10 to 17 years, 3) live in the same household as the target teenager for at least four nights per week in the previous month, 4) have regular access to an android smartphone, and 5) provide written informed consent. If a participant is unable to read or has a severe learning disability that affects their ability to give informed consent, they will not be included for ethical reasons.

For the collection of qualitative data, targeted sampling will be used to identify participants for participation in individual interviews or FGDs (approximately *N* = 30). Participants will be selected based on their level of engagement: low engagement (completing ≤ 4 workshops or modules, *n* = 10); moderate engagement (completing ≥ 5 and ≤ 8 workshops or modules, *n* = 10); high engagement (completing ≥ 9 workshops or modules, *n* = 10).

### Participant timeline

The participant timeline is shown in the study diagram (Fig. 2). Recruitment will rely on our in-country partners, NIMR and ICS, to work with local leaders to identify eligible caregivers. Recruitment pathways of caregivers will be through existing NGO services, schools, and/or individual families needing support. Quota sampling, a non-probabilistic version of stratified sampling [62], will be used to ensure that there is an adequate representation of male caregivers in the sample (approximately 20% males will be recruited per cluster).

**Fig. 2 Fig2:**
[figure not shown]
Study flow diagram

Potential caregivers will be invited to attend an in-person onboarding session where they will be screened for eligibility. Recruitment will continue until full study enrolment of an estimated 40 caregivers is achieved per cluster (October to December 2022). If necessary, recruitment will include peer-to-peer referrals in the community. At onboarding sessions, participants will provide informed consent and receive assistance to install and download the app on their smartphones from trained research assistants. Those who provide informed consent will be considered enrolled. They will then complete the self-administered embedded baseline assessment with support from the trained research assistants. At the end of the onboarding session, digital literacy training will be provided to participants in select clusters. Participants receiving moderated WhatsApp groups will be added to a group within the first week of enrolment. Post-assessments will be completed by participants on their smartphones approximately three months after baseline (January to March 2023) without the presence of a trained research assistant.

### Randomisation and blinding

Cluster randomisation of neighbourhoods (*N* = 16) will involve a single-stage randomisation processes assigning each neighbourhood, i.e., cluster, to one of 8 experimental conditions [63]. Local research managers will send a list of the selected neighbourhoods to a member of the off-site research team prior to randomisation. Random allocation of clusters to experimental conditions will then be conducted using a randomisation algorithm in R. After randomisation, a list of the cluster allocation to experimental conditions will be sent back to the in-country research team. The specific combination of component levels received by caregivers will depend on the onboarding session they attend which is nested within the neighbourhood they were recruited form. Blinding will not be possible for facilitators and local research staff due to their involvement in programme implementation. However, participants will not be informed about the range of possible conditions. The data analyst will be blinded from condition assignment during analysis.

### Measures and outcomes

All quantitative engagement data are derived from the app itself, which tracks app usage throughout the intervention. Socio-demographic and caregiver behavioural measures are derived from a self-administered pre-post questionnaire imbedded within the app. The questionnaire was designed with a dual aim of a) tailoring content to the needs of caregivers (for example using their name, and highlighting workshops/modules that may be particularly important to them) and b) assessing preliminary effectiveness of the programme without being too burdensome and assuming minimal digital literacy. Thus, it only includes items related to the core outcomes ParentApp targets and the most basic socio-demographic information. Items were selected based on a subset of measures previously used in the in-person PLH for Teens implementation in Tanzania [53]. All items originate from open-access measures that have been psychometrically validated in previous studies, including in LMICs. To further ensure that the items were culturally relevant and acceptable in the specific context of our study, we engaged in a co-development process with Tanzanian experts on VAC, conducted iterative pre-piloting with Tanzanian parents, and pilot-tested the measures with 100 Tanzanian families, including both female and male caregivers and their adolescents. We also conducted in-depth qualitative interviews with a subgroup of these families. Where possible, item response scales were standardised to a frequency scale (0 to 8 or more times) to make reading and comprehension easier for participants. Study assessments are summarised in Table 2.

**Table 2 Tab2:**
[figure not shown]
Summary of study assessments

#### Engagement measures

Engagement in digital interventions can be viewed as a three-phase process that is non-linear in nature [64]. In the first phase, participants explore the digital platform to decide if it is useful and relevant. In the second phase, participants use part of the intervention or content. In the third phase, participants return to engage with the content and activities more fully. In this study, we will capture these three phases, while concurrently measuring the amount, frequency, duration, and depth of usage as defined by Perski and colleagues [37]. After reviewing literature, consulting experts, and drawing from experience with engagement and attendance in in-person parenting interventions, the three phases were operationalised as engagement with the app, content, and skills/activities. For each phase, a primary engagement variable was chosen based on its potential impact on parenting practices, while a secondary engagement outcome was selected to assess less commonly measured aspects of engagement. By measuring engagement in this way, we hope to gain insight into how participants engage with the intervention and which variables are most important for achieving desired effects.

##### Primary engagement outcomes (throughout intervention period)

We will assess three primary outcomes, one from each of the three engagement domains outlined above. *Engagement with the app* will be defined as the overall number of app-launches throughout the intervention. *Engagement with the content* will be based on the proportion of workshops or modules completed (out of 12). *Engagement with the skills* will be defined as the proportion of home practice activities started or attempted (out of 10).

##### Secondary engagement outcomes (throughout intervention period)

We will also assess three secondary outcomes, each based on one of the three engagement domains outlined above. *Engagement with the app* will be defined as the overall time spent on the app throughout the intervention. *Engagement with the content* will be the defined as the proportion of workshops or modules started (out of 12). *Engagement with the skills* will be defined as the total number of ParentPoints (self-reported habit tracker) logged throughout the intervention.

##### Other engagement measures

For exploratory and descriptive purposes, additional usage measures may include mode of app use (individual-based or in a group with other caregivers), number of workshops/modules started but not completed, responses to emotional check-ins, dates and times of content accessed, type of content accessed, points of drop-off, and pathways of clicks/navigation. Additionally, engagement with the embedded baseline and endline assessments will be assessed and treated as an outcome of the study. These findings, including retention and dropout rates will be used to inform the forthcoming RCT following the Optimisation Phase of ParentApp.

#### Moderators, co-variates and exploratory outcomes

##### Socio-demographic measures (co-variates, moderators, sample description)

Caregivers will provide information about themselves and their family in the imbedded questionnaire. This will include caregiver gender and age, adolescent age, household size, and one item assessing COVID-related orphanhood (“has a caregiver of your teen passed away in the past three years”). Financial stress will also be assessed using two items adapted from the Financial Self-Efficacy Scale [65]. One item asks, “how many times in the past month have you felt very worried or anxious about money?”. Caregivers respond on a frequency score, on a scale of 0 to 8 or more times. The second item assesses food insecurity “how many days (out of 30) did you run out of money to pay for food?”.

##### Child maltreatment (exploratory outcome, moderator)

Four items adapted from the reduced version of the ISPCAN Child Abuse Screening Tool-Trial Parent Version [66] will be used to assess child maltreatment. The tool asks caregivers to report the frequency of emotional abuse (2 items, “shout, scream or yell” and “insult or call names or stupid”) and physical abuse (2 items, “hitting, spanking or slapping with a hand or with an object like a stick or belt” and “discipline with a push or grab”) over the past month using a scale of 0 to 8 or more times. Items sum to create a score for each subscale as well as a total child maltreatment score.

##### Positive parenting (exploratory outcome, moderator)

Five items from the Alabama Parenting Questionnaire [67] will be used to assess positive parenting. Caregivers will be asked to give a frequency score of their behaviours towards their adolescents in the past month on a scale of 0 to 8 or more times. The tool measures positive parenting (1 item, “how many times have you praised your teen?”), involved parenting (1 item, “get involved in activities that your teen likes”, and parental supervision (3 items, e.g., “stay out in the evening past the time they are supposed to be home”). Items sum to create a total positive parenting score as well as a score for the parental supervision subscale.

##### Parental communication about sexual risk prevention (exploratory outcome, moderator)

Three items adapted from the Parent Teen Sexual Risk Communication Scale III [68] will be used to assess adolescent sexual risk behaviour and caregiver communication about sexual risk prevention. One item asks, “how many times in the past month has your teen walked home alone, taken a lift with someone they don’t know or hung out in a place that made you worried for their safety?”. Caregivers respond on a frequency scale ranging from 0 to 8 or more times. Risk scenarios were adapted based on high-risk scenarios in Tanzania, in discussion with local researchers and based on available evidence. The other item asks, “have you ever talked with your teen about ways to avoid being touched or made to do sexual things with people or online?”. Caregivers respond yes or no. If they respond yes, they will be asked “how many times in the past month have you had a talk like this?”. Caregivers are asked to respond on a frequency ranging from 0 to 8 or more times.

##### Parental depression (moderator)

Three items from the Centre for Epidemiologic Studies Depression Scale (CES-D 10) [69] will be used to assess caregiver depression. The items ask caregivers to respond how they have felt in the previous week (3 items, e.g., “felt that everything you did was an effort”). Caregivers respond on a frequency scale ranging from 0 to 7 days. Items are summed with higher scores indicating greater parental depression.

##### Parenting stress (moderator)

One item adapted from the Parenting Stress Scale [70] will be used to assess caregiver stress. The item asks, “how many times in the past month did caring for your children make you feel very stressed” The items will be rated on a frequency scale of 0 to 8 or more times.

#### Cost outcomes

Costs related to two of the three intervention components will be considered in this study. These include all costs associated with delivering the support component of the intervention, as well as the digital literacy training component. These costs will be collected by the relevant implementing staff using cost diaries. Costs will include money and time spent on programme delivery, i.e. materials and staff-time required for training, preparation, delivery, and coordination of activities. Costs associated with the development of the app are being excluded, since real-world deployments will effectively happen at zero-marginal cost, excluding the cost associated with content adaption. This is because the app has been developed to be completely self-contained, such that no additional supporting infrastructure is needed for routine rollout. In addition, costs incurred by participants (e.g., time spent using the app), and the evaluation of the intervention will be excluded from analyses, as the focus of this study is to understand scale-up cost, feasibility and effectiveness.

### Data collection

Data collected will include digitally tracked engagement data, embedded questionnaire questions, and semi-structured qualitative interviews or FGDs. Questionnaire data includes sociodemographic and pre-post caregiver behavioural questions which are integrated into the first and the last ParentApp workshops/modules. Participants will complete the baseline assessment at the onboarding session, where they can seek support from research assistants. Research assistants have received extensive training from study investigators on interviewing techniques, ethics, and informed consent. All measures will be translated from English to Kiswahili and back translated. Cost data will be collected by research assistants, programme facilitators, coaches, and field coordinators throughout the study.

Interviews and FGDs will be conducted by local researchers with a subsample of participants following semi-structured interview guides. The interview guides are designed to facilitate discussion but remain flexible, allowing for the inclusion of emerging themes during data collection. Interviews and FGDs will be audio-recorded in addition to researchers taking backup notes. Before recording, permission will be sought from all participants, and in situations where the participants decline, notes will be taken. In cases where in-person interviews and FGDs are not possible, remote interviewing via telephone will take place.

Collecting digital engagement data in this trial requires participants to access the internet regularly so that their app activity data can sync with the online server. To improve the quality and accuracy of the data collected, we will provide participants with small monthly data bundles (approximately 1 GB). Additionally, to promote participant retention, participants who complete the questionnaire and semi-structured interview or FGDs will receive compensation for their time (approximately $2 per assessment).

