### Digital interventions as a scalable alternative

With the rapid increase in technology and internet access in LMICs, adaptation of parenting programmes into digital formats has the potential to overcome some of the prominent limitations associated with in-person delivery. Digital parenting programmes, i.e., parenting interventions that use digital technologies to promote behaviour change [27], can be delivered remotely via various platforms including smartphone applications (apps), chatbots, social media, and websites, and range from guided delivery with human support to completely self-guided [28]. These delivery formats may allow for greater scalability, can be accessed irrespective of location and time, and may allow LMICs or underserviced areas to deliver programmes that would otherwise be too costly.

A small but growing number of digital parenting programmes have been tested in high- and middle-income countries to date, with meta-analytic and systematic reviews from high-income countries indicating that they may yield effects comparable to in-person parenting interventions (e.g., [28–33]). However, a major concern that prevents their successful implementation is low engagement by parents. For example, only 7.5% of parents who enrolled in a self-guided online parenting programme in Australia completed all core modules and post-intervention assessments [34]. Looking at the digital intervention literature more broadly, approximately 48% of participants drop out of smartphone mental health intervention trials before the end of data collection [35]. Retention rates are estimated to be even lower in real-world settings. For example, a systematic review investigating real-world uptake and engagement of digital self-help interventions found that while 21% to 88% of participants used the intervention at least once or completed one assessment or module; only 0.5% to 28.6% completed the intervention [36].

As a precursor to behaviour change, poor engagement in parenting programmes may compromise intervention effectiveness [37]. Consequently, low engagement has significant negative implications for population-level public health benefit. Therefore, optimising engagement strategies for digital parenting programmes is crucial to realise their full preventative potential and address the widespread issue of VAC in LMICs.

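### The endline behavioural questions sit in the last workshop/module, so Objective 4 outcomes are observed according to app progress, and the stated three-month date is not secured in the non-sequential app

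*Protocol article*

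**What the plan says.** All references are to the protocol article.

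- **Source of the data.** Measures and outcomes: "Socio-demographic and caregiver behavioural measures are derived from a self-administered pre-post questionnaire imbedded within the app". No endline behavioural data collection outside the app is described.
- **Placement.** Data collection refers to "pre-post caregiver behavioural questions which are integrated into the first and the last ParentApp workshops/modules". Baseline is done at onboarding with staff at hand; the post-assessment is unassisted.
- **Timing.** Participant timeline (text under Fig. 2): "Post-assessments will be completed by participants on their smartphones approximately three months after baseline". No exception by condition is given.
- **Release of content.** In the Component B section, the sequential app is one "whereby a new workshop is made available once every programme week". The non-sequential app lets caregivers take content in any order, with no time gate stated.
- **Recall window.** The child maltreatment and positive parenting items ask about the past month.
- **Incentive.** Data collection: "participants who complete the questionnaire and semi-structured interview or FGDs will receive compensation for their time", at about $2 per assessment.
- **Use.** Objective 4 models the behavioural outcomes with the same mixed models plus their baseline values, and may add mediation by engagement. It is labelled exploratory. Data analysis plans intention-to-treat, with multiple imputation where appropriate.

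**The concern.** There are two linked problems.

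**Observation depends on what is randomised.** A caregiver who never opens the last workshop/module has, as written, no endline. The components were chosen to change how far caregivers progress. The better they work, the more unequal the observed groups become, and a comparison among responders is no longer a comparison of randomised groups. The mediation analysis is the most exposed, because its outcome would be seen mainly where the mediator, engagement, is high.

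**The timing statements do not fit together for half the conditions.** A common three-month date and a questionnaire inside the last module agree in the sequential app. In the non-sequential app there is no defined last module and no stated gate. An endline answered less than a month after baseline would partly describe the period before the programme.

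At stake are the preliminary behavioural findings of Objective 4 and what they suggest for the subsequent RCT.

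**Working it through.** **1. Planned sample.** 16 clusters × 40 = 8 conditions × 80 = 640, so 320 per component level. This reproduces the stated total. The power simulation behind it cannot be reproduced, since its base rates and intracluster correlation are not given. It concerns engagement, so this point does not rest on it.

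**2. How many endlines?** Assumption: response equals completion or retention. The rates come from the Background and Intervention sections.

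| Rate cited | Source described | Responders of 640 | Per condition of 80 |
|---|---|---|---|
| 0.5% | real-world review, lower end | 640 × 0.005 ≈ 3 | 0.4 |
| 7.5% | one self-guided parenting programme | 640 × 0.075 = 48 | 6 |
| 25% | South African pilot, after the first session | 640 × 0.25 = 160 | 20 |
| 28.6% | real-world review, upper end | 640 × 0.286 ≈ 183 | 23 |
| 52% (48% dropout) | smartphone intervention trials | 640 × 0.52 ≈ 333 | 42 |

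The two ends of the review's range come from the statement that "only 0.5% to 28.6% completed the intervention".

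**3. How unequal between levels?** The power section gives odds ratios for the proportion of sessions completed: 2.18 (WhatsApp), 0.48 (sequential) and 2.35 (literacy training). They are used here only as a proxy for reaching the last module. With reference proportion p0, odds1 = OR × p0/(1 − p0) and p1 = odds1/(1 + odds1).

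- p0 = 25%, odds 0.333. OR 2.18 gives odds 0.727, p1 = 0.421: 80 v 135 of 320. OR 0.48 gives p1 = 0.138: 80 v 44. OR 2.35 gives p1 = 0.439: 80 v 141.
- p0 = 7.5%, odds 0.0811. The same steps give 24 v 48, 24 v 12 and 24 v 51.

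**4. Timing.** In the sequential app, 12 weekly releases open the last workshop on day 11 × 7 = 77 or 12 × 7 = 84, which fits about three months. In the non-sequential app the text gives no lower limit. With a 30-day recall window, an endline on day d covers 30 − d days before baseline; at d = 14 (an illustration) that is 16 of 30 days.

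**5. How much bias among responders?** The documents give no response mechanism, so this is a range under assumptions.

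- Outcome Y in SD units, higher meaning better, with no true component effect.
- Latent motivation U, correlation with Y of 0.2 or 0.4.
- logit P(response) = a + γU + ln(OR)·T, with γ = 1 or 2, OR = 2.18 or 0.48, and reference response 7.5%, 25% or 50%.
- Two million simulated caregivers per scenario.

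Results over the 24 scenarios:

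- Difference between component levels: 0.01 to 0.07 SD in absolute size, against the level with more responders. Simulation error is about 0.006 SD where responders are fewest.
- Rejection at nominal 5%: 5.0% to 8.4%, ignoring clustering.
- Responders against all randomised: 0.07 to 0.56 SD.

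A hard-selection case gives more. Suppose the top 10% by motivation respond at one level and the top 20% at the other, with correlation 0.5. The mean of a standard normal in its top 10% is 1.755 and in its top 20% is 1.400, so the difference is 0.5 × (1.755 − 1.400) = 0.18 SD.

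**6. Imputation.** If only caregivers who open the last module can be observed, imputing the rest extrapolates from high engagers. Adding engagement to the imputation model helps only partly until some low-progress caregivers can also answer.

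**The case against.** The strongest reply is that the article does set a common date of about three months, that the assessment table and flow diagram are not visible here, and that how the app triggers the questionnaire is a detail for the full protocol. Embedding was deliberate, to keep burden low, and completion of the endline is itself treated as an outcome. The analysis section foresees dropout and imputation and does not restrict the imputation model to baseline covariates. Tracked engagement is available for it.

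Much of this stands against stronger readings that a reader might infer:

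- **Caregivers in the non-sequential app will answer in week 1.** No text says so. What is stated is a date and a placement that do not fit together.
- **Only caregivers who finish everything can answer.** The article does not say that earlier content must be completed first.
- **Pilot engagement caps the endline at about 160.** The 25% came from a self-guided pilot in another country, before later adaptations. The 48% trial dropout is arguably the closer comparison.
- **The payment contaminates the primary outcomes.** The payment is described without any difference by condition. Opening one module adds roughly a launch and at most 1/12 = 8.3 percentage points of content completion, and whether answering counts as completion is not stated. This is a possible small effect, no more.
- **Component selection is compromised.** Selection uses the engagement main effects, cost-effectiveness based on workshops completed, and qualitative findings. Behavioural outcomes are not used.

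What the reply does not remove is the placement itself. Citing the three-month date restates the conflict, and imputation is a weak remedy while observation is tied to progress.

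**Conclusion.** The point holds, at moderate severity. As written, observation of the Objective 4 outcomes depends on the engagement that the components target, and the timing is not secured in the non-sequential conditions. Bias in the behavioural and mediation analyses is possible, not established. Its direction and size depend on a response mechanism that the documents do not give. Under moderate assumptions it is about 0.01 to 0.07 SD between levels; 0.18 SD needs response to be fully determined by motivation together with a correlation of 0.5, and should not be read as the expected size. Loss of data (about 48 to 183 responders at 7.5% to 28.6%, about 333 at 52%) and unrepresentative responders are the larger harms. The engagement outcomes are tracked by the app and do not use the questionnaire answers.

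**What to change.** Reconcile the Participant timeline, Component B and Data collection sections, and then:

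1. Detach the endline questionnaire from the last workshop/module. Release it to all caregivers in all conditions on a common date about three months after onboarding, whatever their progress, with the same notification and payment.
2. Record the completion date of each endline.
3. Do not count the questionnaire towards launches, time on the app or module completion.
4. Include app-tracked engagement as auxiliary variables in the multiple imputation of behavioural outcomes.
5. Add a missing-not-at-random sensitivity analysis for Objective 4, for example shifting imputed values by a stated range of SDs, separately by component level.

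Cost: a small change of app configuration (scheduled push notifications already exist), some analysis wording, and more $2 payments if response improves. Limit: an in-app questionnaire still reaches only caregivers who open the app, so response will remain partly linked to engagement. Items 4 and 5 are needed for that reason.
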